### Study organisation and randomisation

Nurses at the outpatient clinic at Vrinnevi hospital involved in cardiac rehabilitation will identify eligible patients. The patients will receive information about the study by mail, and then, after about two weeks, will be contacted by a researcher to get personal information about what enrolment in the study could mean. The patients will be given the opportunity to ask the researcher questions about the study.

Patients will be enrolled in the study following baseline assessment and written informed consent. In order to initiate one experiment and one control group, 12–18 patients are needed. Randomisation will be carried out, with sealed unmarked opaque envelopes, which will be assigned to an administrator in a room separate from the research and intervention area. By using a block of 18 study numbers, that will be blindly allocated to either the experiment group (PBL–intervention) or the control group (home-sent patient information)
[45]. The envelopes will contain a card with a unique number from 1 to 185. The administrator will be blinded during the randomisation process. The outcome assessors will be blinded during analysis of new cardiovascular events. The patients and nurses/tutors will not be blinded as the patient education as the PBL education obviously differs from the home-sent information.

### Analysis

All analyses will be conducted according to the intention-to-treat- principle. Appropriate quantitative methods for parametric analyses regarding normally distributed, continuous data will be compared by using e.g. Student’s *t* test and non-parametric analysis for data that is not normally distributed will be performed. The primary variable ‘empowerment to reach self-care goals’ will be evaluated using non - parametric methods, e.g. a Mann–Whitney U test. *P*-values below 0.05 will be considered as statistically significant.

The project started in November 2010 with a pilot study to identify the feasibility of the intervention
[46]. The result of the pilot study was that it was feasible to organize the study in PHC. Fifty-three per cent (n = 17) of eligible patients joined and were randomly allocated according to the design. The pilot study involves a small- scale ethnographic element
[47] with the aim of identifying and describing the enactment of PBL-processes in the experiment group using PBL. The collection of all data in the pilot study (one-year follow-up) was completed in December 2011.

The main study started in September 2011 and the first study patients were included. We are planning to enrol patients during 2011-2014 and follow-up will continue until 2019. The first finding of the COR-PRIM study will become available in 2014, and the first results of the main study around 2015.

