#### Intervention group PBL

These patients will receive PBL patient education in PHC to support self-care (see below), and also conventional care as described above.

The overall goal of the education is to improve self-care through strengthened empowerment

Partial goals are to:

Understand the health benefits of lifestyle changes that the patients want to accomplish

Cope with situations challenging accomplishment of lifestyle changes

Understand and cope with:

Symptoms (angina pectoris, dyspnoea, swelling legs, tiredness)

Changes in diet, physical exercise, medication, psychosocial factors, sexual life

Mental reactions of CHD (depression, anxiety, fear)

Working life (vocational training, stress, dynamic and static work)

Patient education according to the principles of PBL will be provided to a group of 6–9 patients, meeting for a total of 13 occasions for two hours. This will be every week for the first month, then for the next two months there will be two meetings/month and at 16, 20, 26, 39 and 52 weeks after the start. The PBL-intervention will be completed one year after the start.

A PBL model (Figure
2)
[27] supporting the patients learning about self-care will be used. A study guide for the patients will be provided in which learning- and self-care goals may be documented by the patients.

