**Figure 2 F2:**
[figure not shown]
PBL process.

At each meeting the patients use triggers e.g. pictures, texts or concrete materials as starting points for their learning process

District nurses work as tutors after completion of a tutorial education. They support the patients in formulating issues, shared learning goals- and individual self-care goals.

Resource persons, e.g. a physician, physiotherapist, dietician, or social worker, could be invited to respond to questions not solved by the patients themselves. Relatives/family members could also be invited to these meetings.

During the last meeting, focus-group interviews will be performed to collect data about patients’ beliefs, their performance of self-care, and their experiences during the study.

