#### Primary outcomes

The primary outcome is empowerment to reach self-care goals one year after randomisation.

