### Sample size

The sample size was determined for testing whether the difference in mean values between the randomised groups differed from 0 concerning the values in the empowerment instrument, SWE-DES – 23 scale
[31]. The mean value in the group randomised to having home-sent patient information was expected to be 3.0 (standard deviation = 1.2), whilst the analogue value for those randomised to receiving PBL-education, was 3.6 (standard deviation = 1.2). At a significance level of 5% and a power of 80% this yielded the required sample size in each group of at least 63. The clinical significance of 0.6 in the main outcome score is based on the estimation of discriminant validity showing that patients with diabetes, who could be compared with patients with CHD in terms of life-long disease, who reported poor self-rated health scored around 3 in several subscales of SWE-DES – 23 scale; corresponding figures for those who reported good self-rated health was around 0.6 above 3
[31]. Losses to follow up and missing values will, if reasonably random or not too extensive, be taken care of by substituting mean or median values of real data that are typical for the sample
[44]. We will allow for 10% attrition due to losses to follow-up, and death.

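### The named tests and the 63 per arm treat patients as independent although PBL is taught in small tutor-led groups; the primary test should account for PBL group

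*Protocol article*

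**What the plan says.** All references are to the protocol article.

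- **Endpoint (Primary outcomes).** "The primary outcome is empowerment to reach self-care goals one year after randomisation". The PBL programme also ends one year after its start.
- **Test (Analysis).** The primary variable "will be evaluated using non - parametric methods, e.g. a Mann–Whitney U test". Student's t test is the example for normally distributed continuous data. P-"values below 0.05 will be considered as statistically significant".
- **Delivery (Intervention group PBL).** "Patient education according to the principles of PBL will be provided to a group of 6–9 patients, meeting for a total of 13 occasions", each of two hours, over one year. The text under Figure 2 adds: "District nurses work as tutors after completion of a tutorial education". It also says that tutors help patients to formulate learning goals that the group shares, besides individual self-care goals.
- **Control arm (Control group receiving home-sent patient information).** Controls also meet in groups of 6–9, but only at the start and after one year. The material is otherwise mailed.
- **Formation of groups (Study organisation and randomisation).** Each set of 12–18 patients is split at random into one PBL group and one control group.
- **Sizing (Sample size).** The calculation is for "testing whether the difference in mean values between the randomised groups differed from 0", with means 3.0 and 3.6 and SD 1.2. "At a significance level of 5% and a power of 80% this yielded the required sample size in each group of at least 63".

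Neither the Analysis nor the Sample size section mentions PBL group, tutor, ICC or a design effect.

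**The concern.** Patients are randomised one by one, but from then on PBL patients spend 26 hours (13 × 2) with the same few people and a tutor. Correlation created after randomisation is not removed by randomising individuals. The trial's own rationale makes some correlation plausible: the Background gives weight to group education, and the Discussion describes PBL as a group-based method.

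A Mann–Whitney or t test takes its standard error from the number of patients. If outcomes within a PBL group are positively correlated, the PBL arm carries less information than its head count suggests. The standard error is then too small, and a true null effect is declared significant more often than 5% of the time. At stake is the error rate of the trial's main claim, that PBL improves empowerment more than mailed information.

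**Working it through.** **1. Reproduce the 63.** Inputs from Sample size: difference 0.6, SD 1.2, alpha 5%, power 80%.

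n = 2 × [1.2 × (1.960 + 0.842) / 0.6]² = 62.8, so 63 per arm. A one-sided calculation gives 50, so the plan's figure is two-sided. It contains no allowance for grouping: it is the ICC = 0 figure.

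**2. Number of groups.** 165 / 2 = 82.5 PBL patients. 82.5 / 9 ≈ 9 and 82.5 / 6 ≈ 14, so there are about 9 to 14 PBL groups.

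**3. Type I error with grouping in the PBL arm only.** The ICC is not in the documents; 0.02, 0.05 and 0.10 are assumptions. With groups of size m:

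- design effect in the PBL arm, DE = 1 + (m − 1) × ICC; in the control arm, 1
- true variance of the difference divided by the variance the test assumes, r = (1 + DE) / 2
- true error = 2 × [1 − Φ(1.96 / √r)]

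| ICC | DE, m = 6 to 9 | SE too small by factor √r | Error, formula | Error, simulated Mann–Whitney |
|---|---|---|---|---|
| 0.02 | 1.10–1.16 | 1.02–1.04 | 5.6–5.9% | 5.2–6.0% |
| 0.05 | 1.25–1.40 | 1.06–1.10 | 6.5–7.4% | 6.2–7.3% |
| 0.10 | 1.50–1.80 | 1.12–1.18 | 8.0–9.8% | 8.0–9.5% |

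The simulation used 5,000 trials per setting and 72 patients per arm, as 12 groups of 6, 9 of 8 or 8 of 9. A separate simulation of 8,000 trials per setting gave 5.9–6.5%, 7.1% and 8.4–9.1%.

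**4. Allow for shared batch variance.** The PBL and control groups formed from one batch of 12–18 patients may share calendar time and possibly centre. Let b be that variance and g the PBL-group variance, each as a share of a total variance of 1. With equal group sizes the batch part cancels in the difference, so

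r = [(1 − b − g + m × g) + (1 − b)] / 2 = 1 + (m − 1) × g / 2 − b.

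With b = 0.05 (assumed) and m = 7:

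- g = 0.02: r = 1 + 0.06 − 0.05 = 1.01, error 5.1%
- g = 0.05: r = 1 + 0.15 − 0.05 = 1.10, error 6.2%
- g = 0.10: r = 1 + 0.30 − 0.05 = 1.25, error 8.0%

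The 8,000-trial simulation with this batch variance gave 5.0%, 6.2% and 7.4%. With batch variance 0.05 and no PBL-group variance, a simulated test rejects 4.6% of the time, slightly below nominal.

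**5. Power of an analysis that accounts for group.** The plan needs 126 / 0.9 = 140 patients after 10% attrition, and 165 are planned. 165 × 0.9 / 2 ≈ 74 analysed per arm.

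Power = Φ(0.6 / SE − 1.96), with SE = 1.2 × √[(1 + DE) / 74].

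- ICC 0: 86%
- ICC 0.02: 83–84%
- ICC 0.05: 79–82%. For m = 6: SE = 1.2 × √(2.25 / 74) = 0.209, giving Φ(0.91) = 82%
- ICC 0.10: 73–78%

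A noncentral t calculation with Satterthwaite degrees of freedom (11 groups of 7 against 77 controls) gives 86%, 80% and 74% at ICC 0, 0.05 and 0.10. With 10% attrition, the total needed for 80% power is 158–169 at ICC 0.05 and 176–196 at 0.10.

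**The case against.** **The size is assumed.** True. No ICC is given, and nothing in the documents favours 0.05–0.10 over 0.02, where the error is close to nominal.

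**Randomising within batches offsets part of the problem.** This stands. By step 4, inflation disappears once b reaches (m − 1) × g / 2. It is therefore not certain for every positive ICC, though it remains at g = 0.05 with b = 0.05.

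**The article is condensed and the test is only an example.** A statistical analysis plan could handle grouping, and the article does not say that grouping will be ignored. Even so, the tests it names and the sizing it reports both assume independence, and no clustered alternative is offered. This is a choice that can be improved, not a missing detail.

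**The planned number has slack.** The 25 patients above 140 protect power. They do not correct the type I error of an unadjusted test.

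Some stronger readings are tempting but not supported:

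- *The PBL arm has only 9 to 14 independent units.* That holds only at ICC = 1. Eleven groups of 7 (77 patients) are worth 77 / 1.3 ≈ 59 patients at ICC 0.05 and 77 / 1.6 ≈ 48 at 0.10. The number of groups does limit the degrees of freedom.
- *Every interval, outcome and visit is affected.* The Analysis section mentions p-values, not confidence intervals. The group programme ends at one year, and nothing shows group correlation in laboratory or body measures at three and five years.
- *Control groups are equally correlated.* Simulated error would then be 7.7–9.3% at ICC 0.05 and 11.0–13.9% at 0.10. But controls meet only twice, and variance they share with the paired PBL group would cancel. This is an upper case.
- *The PBL groups are closed.* The documents do not say so.

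**Conclusion.** The concern holds for the one-year primary comparison. If outcomes are correlated within PBL groups beyond what the paired control group shares, the plain Mann–Whitney test will usually be anti-conservative. With grouping in the PBL arm only, a nominal 5% becomes about 6%, 7% and 8–9% at assumed ICCs of 0.02, 0.05 and 0.10. With a shared batch variance of 0.05 it becomes about 5%, 6% and 7–8%. The problem is thus small at the low end and material at the high end for a single test judged at 0.05.

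A reader might infer that the trial is underpowered. The figures do not support that up to an ICC of about 0.05, where an adjusted analysis keeps roughly 80% power. At 0.10 power falls to 73–78%.

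These results assume groups of 6–9, equal allocation, normal outcomes with equal total variance and 10% attrition.

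**What to change.** For empowerment at one year, replace the plain Mann–Whitney test with one of these, chosen before outcomes are compared by arm:

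- a clustered rank-sum test, with each PBL group as a cluster and each control as a cluster of one. This is closest to the stated rank analysis. With 9 to 14 groups, its large-sample variance should be checked by simulation.
- a partially nested mixed model with a random intercept for PBL group, randomisation batch as a factor, and Satterthwaite or Kenward–Roger degrees of freedom.

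Use the same approach for the other quantitative outcomes, and report the estimated ICC. State in Sample size that 63 per arm assumes an ICC of 0, and give the range of ICC for which 165 patients still suffice.

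The cost is small. No change to recruitment or delivery is needed; batch and group membership must be kept in the data set. The standard error grows by about 6–10% at ICC 0.05 with grouping in the PBL arm only, and there are fewer degrees of freedom. The mixed model also moves from ranks to means, which is a reason to consider the clustered rank test first.

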Feasibility of the intervention			X		

This table provides an overview of the time schedule of all measurements, and ways to collect data.Questionnaires: Swe-CES-10: The Swedish version of the coronary empowerment scale is a modified version of the Swedish version of the diabetes empowerment scale-23
[31]; GSES: The General Self-Efficacy Scale
[32], NSES: Nutrition Self-Efficacy Scale
[33], PSES: Physical Self-Efficacy Scale
[33], IPAC: International Physical Activity Questionnaire
[34]; Stages of change Scale
[35,36]; Ladder of life
[37,38];Swedish version of EQ5D: EuroQol
[43].Qualitative analysis: Experiences of self-care documented in reflective diary and analysed by critical discourse analysis
[40]; Beliefs of self-care collected in focus groups
[48] and analysed by qualitative content analysis
[39]; enactment of PBL collected by different methods and using ethnographic analysis
[41,42].

Primary and secondary outcome measurements will be assessed at baseline and, at one, three and five years after randomisation.

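### The only test named for the primary outcome makes no use of the baseline score and does not itself estimate the 0.6 mean difference on which the trial was sized

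*Protocol article*

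**What the plan says.** All of this is in the protocol article.

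- **Outcome.** Under Primary outcomes: "The primary outcome is empowerment to reach self-care goals one year after randomisation". This is a level at one year, not a change score.
- **Measurement.** Under Study outcomes and assessment: "Primary and secondary outcome measurements will be assessed at baseline and, at one, three and five years after randomisation". Table 1 lists Swe-CES-10 at all four times.
- **Sizing.** Under Sample size, the calculation is for "testing whether the difference in mean values between the randomised groups differed from 0". The control mean "was expected to be 3.0 (standard deviation = 1.2"), and the value for those "receiving PBL-education, was 3.6 (standard deviation = 1.2"). With 5% significance and 80% power this gives at least 63 per group. The same section adds: "The clinical significance of 0.6 in the main outcome score is based on the estimation of discriminant validity". That estimation was made on SWE-DES-23 in patients with diabetes.
- **Analysis.** The t test is offered for normally distributed continuous data, but the primary variable "will be evaluated using non - parametric methods, e.g. a Mann–Whitney U test", with p below 0.05 as the criterion. The section names no effect estimate and no covariate for this variable.

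**The concern.** The Sample size section works in score points and the Analysis section works in ranks. A reader who wants to know how many points PBL adds, and how uncertain that number is, does not get it from the test that decides the trial. The Mann–Whitney test concerns the ordering of patients between arms.

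The score is also collected before randomised treatment starts, and the named test does not use it. If baseline and one-year scores are correlated, information already collected is left out of the primary comparison. A chance difference between arms at baseline then stays in the one-year comparison.

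At stake are the width of the interval, some power, and a primary result expressed on the scale used in the design.

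**Working it through.** **Inputs from the document:** difference 3.6 − 3.0 = 0.6; SD 1.2; standardised difference d = 0.6/1.2 = 0.5; alpha 5%, taken as two-sided because the document does not say; power 80%; 165 patients, half to each arm; 10% attrition.

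**Assumed:** the correlation r between baseline and one-year score, which the document does not give, and normal scores with equal SD in both arms.

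**1. The plan's own figure.** n per arm = 2 × [SD × (1.960 + 0.842)/0.6]² = 62.8, rounded up to 63. The stated number reproduces, and it is the size for an unadjusted comparison of two means.

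**2. Patients expected at one year.** 165 × 0.9 = 148.5, or about 74 per arm.

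**3. Power of the named test.** For normal data the Mann–Whitney test has efficiency 3/π = 0.955 relative to the t test.

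- At 74 per arm the effective n is 74 × 0.955 = 70.7. Power = Φ(0.5 × √(70.7/2) − 1.960) = Φ(1.01) = 84.4%.
- The unadjusted comparison of means at 74 per arm has power Φ(0.5 × √37 − 1.960) = Φ(1.08) = 86.0%.
- In a simulation with scores limited to an assumed 1–5 range, the rank test has 84.6% and the t test 85.5%.

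**4. What the rank test measures.** Under the design inputs the effect on its scale is P(PBL score > control score) = Φ(0.5/√2) = 0.638. That quantity is not the 0.6-point difference.

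**5. Adding the baseline score.** ANCOVA multiplies the residual SD by √(1 − r²), so power = Φ(0.5/√(1 − r²) × √37 − 1.960). The half-width of the 95% interval is 1.96 × 1.2 × √(2/74) × √(1 − r²) = 0.387 × √(1 − r²).

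| Analysis at 74 per arm | Residual variance removed | Power | 95% CI half-width (points) |
|---|---|---|---|
| Mann–Whitney, as named | – | 84% | – |
| Mean difference, unadjusted | 0% | 86% | 0.39 |
| Adjusted, r = 0.2 | 4% | 87% | 0.38 |
| Adjusted, r = 0.3 | 9% | 89% | 0.37 |
| Adjusted, r = 0.4 | 16% | 91% | 0.35 |
| Adjusted, r = 0.5 | 25% | 94% | 0.33 |
| Adjusted, r = 0.6 | 36% | 97% | 0.31 |

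Exact t calculations are lower by less than half a percentage point (for example 88.6% at r = 0.3 and 93.7% at r = 0.5). No allowance is made for clustering within PBL groups, which is a separate matter.

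**The case against.** The strongest case on the other side is that a journal article condenses the plan, and covariates and estimators are usually settled elsewhere. The Mann–Whitney test is introduced only as an example, so a rank analysis of covariance or a test on change scores is not excluded. A rank method for a short questionnaire score is also defensible. All of this stands, and it limits the point to what the article does fix: sizing on means, a rank approach for the primary variable, and one named test that takes no covariate.

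A reader might infer more, in three ways that the document does not support.

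- **That the trial is underpowered.** At 63 per arm the rank test has about 78% power by the relative-efficiency formula, and about 66 per arm would be needed for 80% (67 by simulation). But 63 is the required minimum, not the planned number. With 165 randomised and 10% lost, about 74 per arm remain and power is about 84%.
- **That the trial could never say whether 0.6 was reached.** A rank test for the p-value does not prevent the reporting of group means and their difference, and a Hodges–Lehmann shift can accompany the test. The planned cost-effectiveness analysis takes the one-year SWE-CES-10 score as its effect measure, which ordinarily needs a between-group difference. What holds is narrower: the named primary test does not itself supply that estimate.
- **That the result would be biased.** Randomisation makes the unadjusted test valid, and chance baseline imbalance averages out over repetitions. Adjustment improves precision; it does not repair an invalid test.

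The gain also depends on r. At r = 0.2 it is small, and a low value is possible because a year-long programme separates the two measurements.

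**Conclusion.** The point holds as a recommended improvement, not as a defect in validity or in size. The named test leaves the baseline score unused and does not estimate the quantity on which the trial was designed.

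Compared with the named test at 74 per arm, the baseline-adjusted mean difference gains about 3 percentage points of power at r = 0.2 (84% to 87%), about 10 at r = 0.5 (84% to 94%), and about 12 at r = 0.6 (84% to 97%). Under normality about 2 of these points come from moving from ranks to means (84.4% to 86.0%), and the rest from the baseline score. The figures rest on the design SD of 1.2, the design difference of 0.6, 10% attrition, an assumed r, and no clustering.

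One caveat applies to interpretation under any analysis: the 0.6 was derived on SWE-DES-23, while the outcome is SWE-CES-10.

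**What to change.** State that the primary estimate is the difference in mean SWE-CES-10 at one year, PBL minus home-sent information, adjusted for baseline SWE-CES-10 by ANCOVA and reported with a 95% confidence interval. Use robust standard errors if the residuals call for them. Keep the Mann–Whitney test as a sensitivity analysis. Where the interval is compared with 0.6, say that this benchmark comes from SWE-DES-23 in diabetes.

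This needs no extra patients or measurements, because the baseline score is already in the schedule, and the stated 63 per group need not change. The article reports that the main study had already started, so the cost is a dated amendment, recorded before outcome data are analysed by arm.
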